**Fig. 1 Fig1:**
[figure not shown]
Design of the MOBILE trial

The participants in the intervention condition will receive motivational counselling (i.e., one home visit and up to two phone calls) from a trained physiotherapist with the focus of individual mobility goals. Participants in the control condition will be receiving written information on health and mobility.

#### Adaptions due to Corona-pandemic

As the Covid-19 pandemic is both unpredictable and dynamic, changes in the execution of the intervention and questionnaires at T_0_, T_1_, and T_2_ may become necessary. If the situation requires it, we will switch to remote option for the aforementioned tasks. To minimize the risk of infections in general, all contacts with participants will take place in compliance with hygiene regulations of Charité – Universitätsmedizin Berlin and federal state of Brandenburg. Key components of the MOBILE hygiene concept include full vaccination of study personal, wearing FFP2-masks, sanitizing, and ventilation at scheduled intervals. Although protocol deviations may occur due to the pandemic, the main components of the trial, i.e., assessment of study variables and delivery of the intervention will still be feasible, albeit with adjustments, such as telephone instead of personal interviews.

### Participants, interventions, and outcomes

#### Study setting

The MOBILE trial will be conducted in the Havelland region, a rural area in Brandenburg, in the eastern part of Germany next to Berlin, Germany. The region Havelland is characterized by mainly flat landscape, vast areas of forest land, stretches of water, and farming, and a generally low population-density with about 150,000 inhabitants. The study centre is located at the Institute of Medical Sociology and Rehabilitation Science, Charité – Universitätsmedizin Berlin.

#### Eligibility criteria

Participants will be included, if they fulfil all inclusion criteria and none of the exclusion criteria, which are as follows. Inclusion criteria are:living in region Havelland, Brandenburg, Germany,75 years or oldercommunity-dwellinghaving sufficient mobility (i.e., being able to move autonomously or with walking devices and/or little help of others),ability tfo give informed consentare willing to participate.Exclusion criteria are:severe cognitive impairments, that prevent living independentlyacute severe events within the past 4 weeks (e.g., falls, operation), that influence out-of-home mobilityinsufficient understanding of German language,severe impairment in vision or hearing that will avert participant’s ability to follow the instructions of the study personnelreasons of exclusion will be recorded and reported.

#### Intervention

The intervention is designed as a tablet-assisted motivational counselling intervention to enhance out-of-home mobility. Summarized it consists of one goal setting and two goal adaption sessions delivered by either one of the two physiotherapists of the study group. All sessions are complemented by the “MOBILE-Intervention-App” (iOS) which is operated by the physiotherapist and works as a documentation and visualization tool. The app was developed by our study team to assist needs of the intervention performance and screenshots of the three main screens of the MOBILE-Intervention-App are depicted in Fig. 2 . Main goal of this intervention is to set and adapt individual goals (e.g., going for a walk, participating in group activity) to foster out-of-home mobility of the participant. All sessions are delivered by the same physiotherapist to rule out information deficits. Couples can take part in the study and are allocated in the same group with each partner receiving separate assessments (T_0_-T_5_). Regarding the intervention, however, there is no strict protocol and couples can either participate together or separately according to their personal preferences and needs. Even when a couple is choosing a joint intervention, mobility goals can still be personalised for each partner and individual profiles are generated in either way. Details of the intervention sessions are described in the following sections and are further classified according to the Behavioural Change Technique Taxonomy (BCT v1) [21]. The BCT Taxonomy was developed by Michie et al. and can be used as a guidance for comparable reporting of complex behavioural interventions. We expect no harms of the intervention and there will be debriefing after the trial.

**Fig. 2 Fig2:**
[figure not shown]
Outline of the Mobile-Intervention-App

#### Goal setting (IV_1_)

After the introduction, overview of the study scope, and relationship establishment, the importance of mobility in old age in terms of social, physical, and mental benefits will be highlighted by the physiotherapist *(BCT: information about health consequences 5.1, information about social and environmental consequences 5.3; see* [21])*.* Both physiotherapists are trained on activating positive und relativizing negative views on ageing and mobility by reframing arising negative automatic thoughts and by representing a general age-appreciating attitude *(framing/reframing 13.2)* [22, 23]. The training consisted of extensive literature research, peer-to-peer counselling, and development of a “learning guide”. The latter is composed of a handbook that will help guiding through the sessions and will be amplified and adjusted by the study group during the scope of intervention.

The main objective of the first session is the setting of individual mobility goals *(goal setting (behaviour) 1.1, goal setting (outcome) 1.3)* in relation with social network analysis *(social support (practical) 3.2, social support (emotional) 3.3)* and linking regional services and opportunities for mobility *(social support (unspecified) 3.1, action planning 1.4).* This will be done by firstly filling out the personal network map (Screen 2) to illustrate existing resources. In a second step, a regional network map with existing opportunities for activity engagement is demonstrated (Screen 3) to point out environmental/social resources and link them with the planned goals (Screen 1). The database underlying the regional network map was generated by the study group prior enrolment and is updated on a regular basis. After illustrating both personal and environmental/social resources, individual mobility goals are discussed and recorded in the intervention app (Screen 1). It is planned to intended at least two distinct mobility goals: One of them being a routine goal (e.g., going for a walk every Monday morning) *(action planning 1.4, habit formation 8.3*) and the other one being a goal with a specific destination (e.g., going to a museum, *action planning 1.4*) that is asked to be routine as well, yet this is not mandatory. It is important to note that a defined goal can also be maintaining the current mobility status (*focus on past success 15.3)*, as maintaining mobility is important for prevention of frailty despite possible decline in physical capacities in old age. Any foreseeable barrier that may impede goal achievement will also be discussed (e.g., loss of physical capacity, pain, environmental challenges) *(action planning 1.4)*. Goal selection and strategies to attain the goals will be set and explored based on the assumption of the selection *(goal setting (behaviour) 1.1, goal setting (outcome) 1.3, action planning 1.4)*, optimization *(commitment 1.9)*, and compensation *(coping planning 1.2)* (SOC) approach [24]. All screens can be printed out directly during the session by using a battery-printer with internal Wi-Fi to ensure that printing works everywhere (i.e., Canon Pixma TR150). This will enhance recognition of the first session, as the participants can keep record of the conversation. The first session will take approximately 60 to 90 min and a new appointment for the following session will be scheduled individually within four weeks.

#### Goal adaption (IV_2_ and IV_3_)

The booster sessions will be performed as telephone interviews and focus on goal adaption and habit formation. The foundation of these sessions are the defined mobility goals that have been established in the first interview. For easy and simple guidance, the outlines of the personal network map and mobility goals that were printed out at the first intervention session are used. The personal network map and each goal will be individually reviewed and discussed regarding whether it was well chosen or if any unexpected barriers occurred *(review behaviour goal(s) 1.5, feedback on behaviour 2.2)*. Goal adaption will then be individually and flexibly adjusted to personal circumstances *(action planning 1.4, coping planning 1.2)*. Moreover, these sessions should not only focus on barriers or optimization but also affirm and encourage *(focus on past success 15.3)* on goals that worked well, especially when the goal is maintaining the current mobility status. A further focus of the follow-up sessions is to transfer the chosen goals into habitual routines of out-of-home mobility (8.3 habit formation). A documentation of the goal adaption session is sent to the person´s home if major modifications have been made. Time needed for each goal adaption session will be about 30 to 45 min.

#### Control condition

The control condition will receive a booklet containing general health information *(information about antecedents 4.2, information about health consequences 5.1)* and advice on how to get more active *(social support (unspecified) 4.1)*. This booklet contains eight pages in A5 format and besides general advice on healthy ageing also includes a page featuring local stakeholder that offer mobility-related (group) activities and one page for phrasing individual goals *(goal setting (behaviour) 1.1)*.

Critical events will be reported for both intervention and control condition. In order to ensure participation adherence the study team contacts participants via phone on a regular basis.

#### Outcomes

## Primary outcome

The primary outcome variable is “time out-of-home” (TOH) based on the objective GPS measurement and meaning the total time spent outside of one´s home radius (i.e. 50 m) per day. TOH can be measured in minutes or percentage. A day in this connection is defined from 3:00 AM to 02:59 AM to include trips than last longer than midnight and as recommended in literature [25, 26]. GPS data is monitored on seven consecutive days at T_0_, T_1_, and T_2_ respectively. An overview of all outcomes, assessments and time of measurement is demonstrated in Table 1.

## Secondary outcomes

Aggregated GPS data: Raw GPS data can be aggregated to certain parameters to describe someone´s life-space. Here we use “convex hull”, a descriptive measure to specify the area of all daily GPS fixes [25]. We will further acquire other variables (such as time first moved, standard deviational ellipse, maximum distance of home) that have been identified as important in literature [7, 25, 27]

Self-perceived life-space mobility: This is measured using the German version of the University of Alabama Life-Space Assessment [8], that has been translated and validated for the use in urban and rural settings by our study group prior to the MOBILE trial [28]. The life-space is assessed both at times of assessment (T_0_, T_1_, and T_2_) on a weekly basis and during the seven-day GPS tracking on a daily basis as part of the activity diary.

Physical activity: Physical activity is assessed using the International Physical Activity Questionnaire (IPAQ) in the short version for older adults [29]. This short version consists of four questions addressing both the number of times per week and minutes per days of strenuous activities, moderate activities, walking, and sitting. A score is then generated and the categories of high, moderate, and low level of activity are composed.

Depressive symptoms: Depressive symptoms are addressed using a validated shorter version [30] of the Geriatric Depression Scale [31]. In the shorter version for residential study population, 12 dichotomous questions are asked and a score is then evaluated.

Health status: The international approved Short-Form 12 (SF-12) [32] of the 36-item short-form health survey (SF-36) [33] is used to measure the subjective overall health status for the last seven days.

Operationalisation of Frailty: The used Frailty phenotype approach is based on a cluster of five clinical criteria (reduced muscle strength, slow gait speed, exhaustion, weight loss, low level of physical activity) developed by Fried et al. in 2001 [34]. This phenotype is one of the most popular tools to evaluate frailty, predict adverse health outcomes and distinguishes well between three different stages of frailty (robust, pre-frail, frail) in older adult [34, 35]. To rate the physical criteria of the phenotype, functional tests are performed using the SAHEAN 5001 hand grip dynamometer to assess handgrip strength [34] and a 3 m walking test in preferred speed to measure gait speed [36]. To assess the criterion of exhaustion two questions of the Centre for Epidemiological Studies depression (CES-D) scale are used like in the original publication by Fried et al. and weight loss was defined as unintentional weight loss of ≥ 5 KG in the prior year [34]. The criterion of low physical activity is retrieved from a single item question of the validated SHARE-frailty phenotype Instrument [37].

Mediators and covariates are also outlined in Table 1 and contain personal, social, and environmental resources.

### Sample size

For the sample size calculation, results of previous intervention studies for increasing mobility in older adults were considered [38, 39]. A relevant change in mobility is considered as an increase in mobility of 15% after three months (Life Space *M* = 65.4 (*SD* = 20.1) + 15% = 75.2 [40] in comparison to the control condition (1:1 ratio, power 1 – beta = 95%, alpha (two-sided) = 5%, dropout = 15%). Based on these presumptions an online tool (powerandsamplesize.com) has been used to calculate sample size, which is stated as follows: *N* = 110 + 15% dropout in each condition and therefore a total sample size of *N* = 254 (*N* = 127 in each condition) is needed.

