#### Statistical analysis

Raw GPS data will be checked and aggregated by a computer scientist of the TU Berlin und will be prepared for further analyses. All analyses will be performed using SPSS v25 (IBM, Cary, Inc.) and in R Project using the intention-to-treat principle. For the demographic variables, means, standard deviations and frequencies will be calculated, and distribution will be checked. Medians and interquartile ranges will be reported for non-normally distributed data. To test the primary hypothesis, multilevel modelling will be used to estimate the group difference in the primary outcome across T_0_-T_2_ as predefined in the power analysis. Covariance analysis will also examine possible mediating variables declaring any relationship between out-of-home mobility and individual resources. The level of significance will be set to p < 0.05 (two-sided) and 95% confidence interval will be reported. Multiple imputations using a package (e.g., AMELIA II) will be applied to handle missing data if necessary.

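### The sample size and 95% power are derived for a Life Space score; no power is stated for the primary outcome, GPS time out-of-home

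*Protocol article*

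**What the plan says.** The Sample size section sets the target as follows: "A relevant change in mobility is considered as an increase in mobility of 15% after three months". The figures behind it are "Life Space *M* = 65.4 (*SD* = 20.1) + 15% = 75.2". The comparison is "in comparison to the control condition (1:1 ratio", with 95% power, "alpha (two-sided) = 5"% and 15% dropout. The result is 110 per arm before dropout, 127 per arm after it, and 254 in total.

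The Primary outcome section names a different variable: time out-of-home per day, "based on the objective GPS measurement", expressed in minutes or as a percentage. Table 1 and the abstract agree. Both place life-space measures (the GPS convex hull and the self-reported LSA-D) among the secondary outcomes. The Secondary outcomes section identifies the questionnaire as the "German version of the University of Alabama Life-Space Assessment".

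The Statistical analysis section plans a multilevel model for the group difference in the primary outcome over T0 to T2, "as predefined in the power analysis".

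**The concern.** A power figure belongs to one outcome, one difference and one SD. Here all three come from a Life Space score, while the test that decides the trial is on GPS time out-of-home. A 15% change equals 0.49 SD only because that score has an SD/mean ratio of 0.31. The article offers no argument that the ratio, or the standardised effect, carries over to minutes out of home. Its own Background and Discussion treat GPS and self-report as distinct ways of measuring mobility, so the transfer cannot be taken for granted.

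What is at stake is how the result will be read. As printed, a null finding on time out-of-home would be taken as a negative from a trial with 95% power to see a 15% change. The article contains nothing that supports that reading.

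**Working it through.** **Step 1: reproduce the stated size.** Inputs from the Sample size section: mean 65.4, target 75.2, SD 20.1, two-sided 5%, power 95%, ratio 1:1.

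- Difference: 75.2 − 65.4 = 9.8. Standardised: 9.8 / 20.1 = 0.488. SD/mean: 20.1 / 65.4 = 0.307.
- n per arm = 2 × (20.1 / 9.8)² × (1.96 + 1.645)² = 109.3, rounded up to 110.
- Dropout: 110 × 1.15 = 126.5, rounded up to 127 per arm, 254 in total.

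The stated figures reproduce from the Life Space inputs alone. With 127 randomised and 15% lost, 127 × 0.85 = 107.95, about 108 per arm, remain. Power for the Life Space difference is then still about 95%, so the way dropout was added does not matter here.

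**Step 2: look for the same inputs for time out-of-home.** The article gives no mean, SD, relevant difference or power for it. No single corrected figure can be computed.

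**Step 3: show how far the answer depends on what is missing.** Assumptions, none of them in the article: the relevant change in time out-of-home is also 15% of the mean; its SD/mean ratio takes the values below; where baseline is used, the baseline-to-follow-up correlation is r = 0.7.

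- Unadjusted at one time point: d = 0.15 / (SD/mean).
- Baseline-adjusted: d = 0.15 / [(SD/mean) × √(1 − r²)], where √(1 − 0.49) = 0.714.
- Power ≈ Φ(d × √(108/2) − 1.96). The table uses the two-sample t version, which differs by less than half a percentage point.

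Example at SD/mean 0.5, unadjusted: d = 0.30, 0.30 × 7.348 − 1.96 = 0.245, power about 59%. Adjusted: d = 0.30 / 0.714 = 0.420, 0.420 × 7.348 − 1.96 = 1.13, power about 87%.

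| Assumed SD/mean | Power, unadjusted | Power, adjusted (r = 0.7) |
|---|---|---|
| 0.31 (Life Space value) | 95% | 99.9% |
| 0.4 | 78% | 97% |
| 0.5 | 59% | 87% |
| 0.6 | 45% | 73% |
| 0.8 | 28% | 48% |

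**Step 4: where 95% would hold.** With 108 per arm, the difference detectable at 95% power is 3.605 × √(2/108) = 0.491 SD. A 15% change reaches that if SD/mean is at most 0.15 / 0.491 = 0.31 unadjusted, or at most 0.15 / (0.491 × 0.714) = 0.43 with adjustment at r = 0.7. The article does not say on which side of these limits time out-of-home lies.

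**The case against.** The planned analysis is a multilevel model over T0 to T2, which uses the baseline week. An unadjusted t-test understates its power, and at an assumed correlation of 0.7 the gain is large. This stands, and is why both columns are shown. The correlation is itself an assumption, however, and cannot be known from baseline data alone.

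The Sample size section speaks of mobility in general and never writes LSA-D or self-reported, so calling the sizing variable the questionnaire score is an inference. That also stands, but it does not rescue the calculation. The only life-space measures in the article are the questionnaire and the GPS-derived area parameters. All are secondary, and none is time out-of-home.

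The cross-reference to the power analysis could be read as pointing only to the between-group contrast and the three-month horizon, both of which are in the Sample size section. That reading is possible. The sentence still attaches the power analysis to the primary outcome, and a reader will carry the 95% with it.

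A reader might go further and infer that the trial is underpowered, that a real 15% increase would probably be missed, or that more participants are needed. The article supports none of these. It does not show that time out-of-home is relatively more variable than the Life Space score. Even unadjusted, power exceeds one half at assumed ratios of 0.4 and 0.5.

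**Conclusion.** The point holds in a limited form. The 254 participants and 95% power are correct arithmetic for a 0.49 SD difference on a Life Space score, which is not the primary outcome. For GPS time out-of-home no power is stated, so the 95% is unsupported for the primary test. True power could be lower or higher. Over the assumed ranges it runs from 28% to 99.9%, depending on the SD/mean ratio and on how much the baseline week explains. That spread measures what the article leaves open and is not an estimate of the trial's power. This goes beyond an omission that a fuller document might supply, because the article prints a complete calculation on another variable and then links the primary analysis to it.

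**What to change.** 1. In the Sample size section, state that N = 254 and 95% power apply to the Life Space score (difference 9.8, SD 20.1), and name the instrument.
2. In the Statistical analysis section, correct or remove the phrase that ties the primary-outcome model to the power analysis.
3. Estimate the mean and SD of time out-of-home from the T0 GPS weeks as they accrue (the Trial status section shows recruitment still running), pooled over arms and blind to allocation. The article already keeps the GPS analysts blinded.
4. For N = 254, restate the power for a 15% change in time out-of-home and the detectable difference in minutes per day. Do this under the planned model that uses baseline, over a stated range of baseline-to-follow-up correlations, since T0 data cannot supply that correlation.

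The cost is two wording changes and a short blinded calculation. The purpose is to restate the figure, not to enrol more. The downside is that the stated power may turn out less favourable than 95%.

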**Methods:**

In the MOBILE randomized controlled trial, we plan to enrol 254 community-dwelling older adults aged 75 and older from Havelland, a rural area in Germany. The intervention group will receive a tablet-assisted motivational counselling at the participant´s home and two follow-up telephone sessions. Main focus of the counselling sessions lays on setting and adapting individual mobility goals and applying action planning and habit formation strategies by incorporating the personal social network and regional opportunities for engaging in mobility related activities. The control group will receive postal general health information. The primary mobility outcome is time out-of-home assessed by GPS (GPS.Rec2.0-App) at three points in time (baseline, after one month, and after three months for seven consecutive days each). Secondary outcomes are the size of the GPS-derived life-space convex hull, self-reported life-space mobility (LSA-D), physical activity (IPAQ), depressive symptoms (GDS), frailty phenotype, and health status (SF-12).

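### The 15% dropout allowance is added to 110 rather than divided out, so 254 enrolled leaves about 108 per arm, not 110; the power cost is very small (about 94.8% against 95.1%)

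*Protocol article*

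**What the plan says.** The Sample size section of the protocol article gives all the inputs in one place. The effect is "an increase in mobility of 15% after three months", worked out on a Life Space score as "Life Space *M* = 65.4 (*SD* = 20.1) + 15% = 75.2", and it is judged "in comparison to the control condition (1:1 ratio"). The error rates are "alpha (two-sided) = 5"% and "power 1 – beta = 95"%, and dropout is assumed to be 15%.

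The result is "110 + 15% dropout in each condition and therefore a total sample size of" 254, with "127 in each condition) is needed". The abstract repeats the total as the enrolment target: "we plan to enrol 254 community-dwelling older adults aged 75 and older". The section states no other margin or allowance.

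**The concern.** The figure of 110 is the number that must be available for analysis if the comparison is to have 95% power. An allowance for 15% dropout should give an enrolment from which 110 remain once 15% of those enrolled have been lost. Adding 15% of 110 does not do this, because the loss applies to the larger enrolled number.

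At stake is whether the headline figure is consistent with its own assumptions. The total of 254 is described as the number needed, and under Trial status recruitment may be extended if the required number has not been reached. The figure is likely to be repeated in the trial report, where a reader can check it by hand.

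**Working it through.** **Inputs, all from the Sample size section:** mean 65.4, SD 20.1, target mean 75.2 (difference 9.8), 1:1 allocation, two-sided alpha 0.05, power 0.95, dropout 0.15.

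**Step 1: reproduce the 110.** The normal-approximation formula for two means is

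n per arm = 2 × SD² × (z₀.₉₇₅ + z₀.₉₅)² / difference²

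= 2 × 20.1² × (1.960 + 1.645)² / 9.8² = 109.33, rounded up to 110.

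With the unrounded difference (15% of 65.4 = 9.81) it gives 109.11, again 110. A one-sided test would give 92. The plan's 110 is therefore confirmed as the evaluable number per arm.

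**Step 2: reproduce the 127.** 110 × 1.15 = 126.5, rounded up to 127; 2 × 127 = 254. This matches exactly, so the allowance was added as a percentage of the evaluable number.

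**Step 3: apply the stated dropout to the stated enrolment.** 127 × 0.85 = 107.95, about 108 per arm. In total 254 × 0.85 = 215.9, against 220 required.

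**Step 4: the enrolment that leaves 110.** 110 / 0.85 = 129.4, rounded up to 130 per arm, 260 in total. Check: 130 × 0.85 = 110.5, whereas 129 × 0.85 = 109.65 falls just short.

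**Step 5: power, by the formula of step 1.** Power = Φ(difference/SD × √(n/2) − 1.960).

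| Evaluable per arm | Power (normal approximation) |
|---|---|
| 110 | 95.1% |
| 108 | 94.8% |

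The like-for-like loss is about 0.3 percentage points.

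**Step 6: the dropout that 254 can bear.** The loss that leaves exactly 110 of 127 is 1 − 110/127 = 13.4%. The loss at which power falls to exactly 95% is slightly higher, because 110 was itself rounded up: 1 − 109.33/127 = 13.9%. Both are below 15%, so rounding up to 110 does not absorb the gap.

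**The case against.** Several things can fairly be said for the plan.

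- **The effect is trivial.** About 2 evaluable participants per arm are lost, and 94.8% rounds to 95%. This is right and sets the weight of the point, but it does not make 254 follow from the stated inputs.
- **The rule is shown openly.** The section writes the allowance as an addition, and never says outright that 110 remain after the loss. That is so. But it lists 15% dropout and 95% power together as assumptions and calls the resulting total needed, and under those assumptions 254 is not enough.
- **Dropouts need not be lost entirely.** The Statistical analysis section plans an intention-to-treat multilevel model across T0 to T2, with multiple imputation if necessary, so someone lost before T2 can still contribute data. This stands as a caution against reading actual power from the number of completers. The sample size calculation takes no credit for it, however, so the nominal shortfall remains.

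A reader might also infer more than the document supports. A t-based calculation gives 94.6% at 108 per arm, and setting that against the planned 95% makes the loss look larger. But the same t calculation gives only 94.9% at 110, so part of that gap is the difference between formulas and has nothing to do with dropout. The 110 comes from the normal formula, and the comparison should stay within it.

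**Conclusion.** The point holds as a small arithmetic error. The stated total of 254 is 6 below the 260 that its own inputs require. With 15% dropout it leaves about 108 per arm instead of 110, with power of about 94.8% instead of 95.1%.

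This rests on the section's own Life Space assumptions (difference 9.8, SD 20.1), on a two-group comparison at three months, and on dropouts contributing nothing to it.

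Two stronger readings are not supported. The error does not make the trial underpowered in any practical sense. Nor do these power figures describe the primary comparison itself: the primary outcome is GPS-measured time out-of-home, for which the article gives no SD, and the planned model differs from the two-sample formula. The figures show only whether the sample size sentence agrees with itself.

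**What to change.** Keep the enrolment at 254 and correct the sentence in the Sample size section, for example: 254 enrolled (127 per arm) retains 110 per arm with up to 13.4% dropout; with 15% dropout about 108 per arm remain, giving about 94.8% power under the same Life Space assumptions.

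The 13.4% should be described as the loss that leaves 110 per arm, not as the exact limit for 95% power, which is about 13.9% by the same formula. The t-based 94.6% should not be set against 95%.

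The cost is one sentence, carried into the trial report. If the team prefers to keep both 15% dropout and 110 per arm as stated, the total becomes 260, which means 6 more participants; the size of the shortfall does not require it.
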